#### Health-related quality of life

Health-related quality of life will be assessed 3, 6 and 12 months after randomisation by using the EQ-5D-5L and VEINES-QOL/Sym. The EQ-5D is a generic measure of health status, in which health is characterized on five dimensions (mobility, self care, ability to undertake usual activities, pain and anxiety/depression) [18]. Participants will be asked to describe their level of health on each dimension by using one of five levels: no problems, slight problems, moderate problems, severe problems or extreme problems. The EQ-5D has been validated in the UK and was used in the Venous leg Ulcer Study III (VenUS III) and VenUS IV trials [5, 30]. The VEINES-QOL/Sym is a disease-specific quality-of-life instrument for use in venous diseases of the leg [19].

#### Lower-limb cutaneous microvascular function

Laser Doppler fluximetry and iontophoresis will be used to assess cutaneous microvascular function [31] in the gaiter area of the affected leg. We will assess areas of skin that are in close proximity to the ulcer but at least 3 cm away from the edge of the ulcer. Assessments will be performed in a temperature-controlled room (22–24 °C) with the participants in a supine position and the leg elevated at 30°. Compression garments will be removed only if patient care is not compromised (e.g., removable compression stockings are worn). Heart rate (Sports Tester; Polar, Kempele, Finland) and blood pressure (left arm; Dinamap Dash 2500; GE Healthcare, Wauwatosa, WI, USA) will be monitored at 5-minute intervals throughout the protocol. The two drug delivery electrodes (PF383; Perimed AB, Jarfalla, Sweden) will be positioned over healthy-looking skin, approximately 4 cm apart; one will contain 100 μl of 1 % acetylcholine chloride (ACh) (Miochol-E; Novartis, Stein, Switzerland) and the other 80 μl of 1 % sodium nitroprusside (SNP) (Nitroprussiat; Rottapharm, Monza, Italy), and de-ionised water will be used as the solvent. A battery-powered iontophoresis controller (PeriIont PF382b; Perimed AB) will be used to provide the charge needed for the simultaneous delivery of ACh and SNP. A 4-minute stable recording of baseline flux will be followed by administration of the two agents in accordance with the following protocol: 0.2 mA for 10 seconds (i.e., 2 mC), 0.2 mA for 15 seconds (i.e., 3 mC), 0.2 mA for 20 seconds (i.e., 4 mC), and 0.3 mA for 20 seconds (i.e., 6 mC), with 4-minute intervals between each dose. To obtain an index of skin blood flow, cutaneous red cell flux will be measured by placing an iontophoresis laser-Doppler probe (PF481-1; Perimed AB) connected to a laser Doppler fluxmeter (PF5001; Perimed AB). Responses to ACh and SNP will be used as indicators of the changes occurring in the endothelial-dependent and -independent vasodilatory function, respectively. The process will be repeated in the gaiter area of the non-affected leg following a 10-minute resting period.

#### Physical fitness – Senior Fitness Test

The Senior Fitness Test is a widely used test battery for evaluating the effects of exercise interventions in older adults and consists of six sub-tests which measure the physical abilities needed to perform activities of daily living [21]. However, three of the sub-tests—for upper-body flexibility, upper-body strength, and agility—will not be used, as these aspects of physical fitness are not targeted within the exercise intervention. Therefore, the tests used in this trial will be (i) 30-second chair-stand test for lower-body muscular strength and endurance (the number of times in 30 seconds a participant can stand fully from a seated position without using their arms), (ii) chair sit and reach test for lower body flexibility (from a sitting position at front of chair, with leg extended and hands reaching toward toes, the number of centimetres (+ or −) between extended fingers and tip of toe), and (iii) the 6-minute walk test for aerobic fitness (the maximum distance a participant can walk in 6 minutes). All tests will be measured once, except the sit and reach tests, which will consist of a practice, then two trials. The Senior Fitness Test has acceptable test-retest reliability (R = 0.81–0.98) and construct validity against a range of indicators, such as age and exercise status, and criterion validity (r = 0.71–0.82) [32].

#### Adherence to background clinical therapies

All participants will be asked to complete specially developed, self-reported diaries for their adherence to leg elevation instructions, usage of compression therapy and contact time with the tissue-viability nursing team to assist the full-study and health-economic analysis. This procedure will be supported by weekly phone calls from a research team-member at all stages.

### Health economics

The broader aim is to undertake a comprehensive cost-utility analysis with both NHS and societal perspectives. However, in this feasibility study, the primary objective is to account for as well as make fair assessment and valuation of costs (direct and indirect costs) and benefits (quality-adjusted life-year (QALY) gains) as a result of the 12-week exercise intervention. The major cost drivers will be patient’s use of NHS and private health services, the patient’s time and their travel costs and intervention delivery costs.

#### Cost of intervention

This will include staff time, including exercise instructor related to intervention delivery, resources and equipment used and room costs as well as any incentive given to patients to adhere to the exercise session.

#### Costs to patients in the intervention group

This will be based on the distance to the exercise training facility and travel costs, time taken off from work to attend the exercise session and any additional equipment/aids/shoes and bandage/dressing purchased to undertake exercise sessions.

#### Difference in resource use between intervention and control groups

The resource use questionnaire will be completed by intervention and control groups at 3-, 6- and 12-month intervals to elicit information on utilisation of NHS and private health-care services related to leg ulcer treatment. It collects information on the number of visits, travel time and cost, and cost to the patient for the following uses: General practitioner; Doctor at leg ulcer clinic; NHS Hospital consultant/specialist; Doctor/nurse at accident and emergency; NHS Physiotherapist; Private Physiotherapist; Private doctor/consultant; Private chiropractor; Psychologist/counsellor; and Any other. Similarly, the number of times and the costs to the patient for undertaking diagnostic tests (e.g., x-rays, computed tomography scan, magnetic resonance imaging scan, blood test and any other tests) and for medications (e.g., pain killers, sleeping pills and antibiotics) and other aids (e.g., compression hosiery or bandages) related to leg ulcer will be collected. Furthermore, number of days of hospitalisation related to leg ulcer and data on costs for any equipment purchased for speedy recovery from leg ulcer will be collected.

#### Difference in time taken off from work between intervention and control groups

The patient’s work status, employment type (full-time, part-time, self-employed, unpaid work, unemployed and inactive) and the number of days off from work because of leg ulcer will be accounted for in presenting the societal perspective on costs and benefits of the intervention. The changes in the employment status because of leg ulcer will be recorded during the intervention and follow-up period.

#### Differences in quality of life between intervention and control groups

The new EQ-5D-5L questionnaire will be used to measure quality of life at baseline and at 3-, 6- and 12-month intervals. Using the standardised general population-based tariff, the scores will be converted into QALYs and then compared between intervention and control groups.

#### Incremental cost-effectiveness ratio

To measure the net effect of intervention, the incremental cost-effectiveness ratio will be derived from relating differences in costs to benefits between intervention and control groups during a 12-month period. We will use standard published sources for unit costs where available and supplement this with local sources if required. We will use the same methods of analysis as in a definitive trial, including imputation methods for missing data, analysis of uncertainty and non-normal distributions: that is, standard statistical analysis of costs will be performed to test for statistical significance of results, while bootstrapping would be performed to estimate the confidence interval (CI) of average interventional costs.

### Qualitative component

The aim of the qualitative component is to explore participants’ experiences of having a venous ulcer and the acceptability of the exercise intervention and study procedures. A sub-sample of 16 participants will be recruited by using purposive sampling (mixture of genders, younger and older participants from intervention and control groups). Semi-structured interviews of up to 1 hour will be conducted with participants either face-to-face or via telephone (participants’ preference) after the 3-month follow-up visit. The following topics will be explored:participants experiences’ of leg ulcerationexperiences of treatment and advice givenparticipants’ preference for trial allocationparticipant acceptability of the exercise intervention and study procedures.

Transcripts will be analysed thematically by using framework analysis as this approach provides a systematic process to analyse qualitative data. The in-depth interview offers an opportunity to investigate in detail participant’s personal perspectives of their leg ulcer experiences set within their personal frame of reference. The interview method also means that there will be time to explore participant’s motivations, attitudes, intervention impact and experiences in greater detail than that afforded by a focus group setting [33]. Framework analysis [34] offers an approach that is somewhat inductive; that is, it is based in the original interview transcripts but framed within the “constraints” of an *a priori* framework. An audio recording of the interviews will be made and then transcribed verbatim, and the five stages of framework analysis (familiarisation, identifying a thematic framework, indexing, charting and mapping) will be followed.

### Statistical analysis

The sample size for a feasibility study should be adequate to estimate critical metrics, needed to assess the feasibility of conducting the definitive study, with sufficient precision. Herein, the critical metrics are the consent rate (i.e., the proportion of eligible patients who consent to participate and be randomly assigned), ulcer-healing rates and compliance with treatment, and attrition. Forty patients in each group will provide a sufficiently precise (within 15 percentage points for a 90 % CI) estimate of the proportion willing to be randomly assigned, assuming 35–40 % intention to be randomly assigned. A sample size for an adequately powered randomised controlled trial will be determined from the results of this trial.

Descriptive statistics will be used to characterise the groups at baseline and to present the feasibility outcomes described above. Although determining differences in clinical outcomes between the two arms is not the primary purpose of this trial, comparisons will be undertaken to investigate the feasibility of studying these outcomes and to calculate estimates for the likely effect sizes and 95 % CIs. Analyses will be conducted in SPSS by using the principles of intention-to-treat. Significance tests will be two-sided at the 5 % level. Healing rates will be compared by using the Kaplan-Meier method. Hazard ratios and 95 % CIs will be presented for ulcer healing time by using Cox regression analysis models. For other outcomes, the intervention and control groups will be compared by using linear or logistic regression (depending on the type of outcome) adjusting for ulcer size and any other important baseline covariate. Relevant assumptions will be checked for all models. For the potential primary outcomes for a definitive trial, the likely effect of the exercise intervention will be estimated via standard intervention minus control comparisons, accounting for the type of variable and its distributional properties. We will examine whether the CIs include potentially clinically important effects in outcomes between groups. As this is a feasibility study, these comparisons are exploratory and are intended to inform the subsequent, definitive trial.

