### Randomisation and masking

After completion of baseline assessments, participants will be randomly assigned 1:1 to an intervention group or a control group. The research assistant will request (via email) a participant’s allocation from the trial statistician (AG) who manages the randomisation schedule. The statistician is not involved in the recruitment or data-gathering processes and is based in a different location to where the study visits are completed. Participants will be stratified by ulcer size (maximum ulcer diameter of either between 1 and 3 cm or greater than 3 cm in any direction) with permuted blocks of variable size, because this criterion is a known predictor of ulcer healing [22]. We could not mask participants or intervention supervisors to the allocated treatment. Outcome assessors will be blinded to group allocation.

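### The Cox and Kaplan-Meier analysis of healing time names no ulcer-size adjustment, although ulcer size is the randomisation stratum and the article says it predicts healing

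*Protocol article*

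**What the plan says.** All references are to the protocol article.

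- **Randomisation and masking:** "Participants will be stratified by ulcer size" (maximum diameter 1 to 3 cm, or above 3 cm), using variable-size permuted blocks. The reason given is that "this criterion is a known predictor of ulcer healing".
- **Statistical analysis, healing:** the first statement is "Healing rates will be compared by using the Kaplan-Meier method". On the regression side, the article then says only that effect estimates with intervals "will be presented for ulcer healing time by using Cox regression analysis models". Neither sentence names a covariate or a stratum.
- **Statistical analysis, next sentence:** "For other outcomes, the intervention and control groups will be compared by using linear or logistic regression". Which of the two is used follows from the kind of outcome, and it is to these models that the article attaches the clause "adjusting for ulcer size and any other important baseline covariate".

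The same section calls the between-arm comparisons exploratory, lists ulcer-healing rates among the metrics that matter for feasibility, and says the definitive sample size will come from this trial's results.

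**The concern.** The article does deal with covariate adjustment. It names ulcer size and says which models receive it, and those are the models for everything except healing time. On a plain reading, fitness and quality of life are adjusted for ulcer size, while the outcome that ulcer size is said to predict is not. The proportion healed at 3, 6 and 12 months, if handled as a binary outcome under the logistic sentence, would be adjusted. Time to the same healing event would not be. The two summaries would then answer slightly different questions.

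Leaving a prognostic factor out of a Cox model moves the treatment HR toward 1 relative to the effect within levels of that factor. Stratified allocation also balances the factor between arms, so a model that ignores it can report a standard error larger than the estimator's real spread. Healing is the subject of the study hypothesis and a natural candidate for the definitive primary outcome, so the HR may be carried forward into planning.

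**Working it through.** **The plan's own precision figure.** It concerns the proportion willing to be randomised, not healing. It reproduces as a bound: 1.645 × √(0.35 × 0.65/40) = 0.124 and 1.645 × √(0.40 × 0.60/40) = 0.127, both within 15 points. The article gives no precision figure for the HR, so the check is a simulation.

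**Inputs from the article.** 80 patients, 1:1, two ulcer-size strata, 12 months of follow-up, a median healing time of 9 to 11 weeks (10 used), loss to follow-up to be below 20% (20% used), two-sided 5% tests.

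**Assumptions.** Exponential healing times; exact 1:1 balance within strata; half the patients with large ulcers; healing HR of large versus small ulcers 0.7, 0.5 or 0.33; within-stratum treatment HR 1.0, 1.5 or 2.0. The article gives none of these HRs.

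**Model.** With a = 1 for exercise and z = 1 for a large ulcer, hazard = (ln 2/10) × HR^a × S^(z − 0.5), where S is the stratum HR. For S = 0.5 the control medians are 10 × √0.5 = 7.1 weeks (small) and 10/√0.5 = 14.1 weeks (large). Each of 3,000 data sets per scenario was fitted three ways: treatment only, treatment plus stratum, and Cox stratified by z.

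**Results at a within-stratum HR of 1.5:**

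| Stratum HR | HR unadjusted | HR adjusted | HR stratified | Model SE unadj. / adj. / strat. | Actual SD of log HR, unadj. | Power unadj. / adj. |
|---|---|---|---|---|---|---|
| 0.7 | 1.496 | 1.519 | 1.511 | 0.238 / 0.240 / 0.243 | 0.241 | 0.385 / 0.403 |
| 0.5 | 1.461 | 1.521 | 1.515 | 0.238 / 0.241 / 0.244 | 0.238 | 0.335 / 0.405 |
| 0.33 | 1.407 | 1.519 | 1.513 | 0.238 / 0.242 / 0.245 | 0.216 | 0.274 / 0.408 |

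A repeat gave unadjusted HRs of 1.50, 1.47 and 1.41 and power of 0.38, 0.35 and 0.28. Monte Carlo error is about √(0.4 × 0.6/3000) = 0.009 for power and 0.24/√3000 = 0.004 for the mean log HR. With 30% large ulcers and stratum HR 0.5, the HRs are 1.463 and 1.520, and power 0.351 and 0.404.

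**At a within-stratum HR of 2.0.** Unadjusted 1.99, 1.92 and 1.80 against about 2.04 adjusted.

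**At HR 1.0.** No attenuation. Unadjusted model SE against actual SD: 0.237 and 0.237 (stratum HR 0.7), 0.237 and 0.222 (0.5), 0.239 and 0.222 (0.33). Rejection rates are 0.047, 0.032 and 0.032 unadjusted, and 0.052, 0.047 and 0.054 adjusted. The unadjusted test is therefore conservative once the stratum effect is more than weak.

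**Interval width.** Ratio of upper to lower limit = exp(2 × 1.96 × SE). At HR 1.5 and stratum HR 0.5: exp(3.92 × 0.2381) = 2.54 unadjusted, exp(3.92 × 0.2407) = 2.57 adjusted, exp(3.92 × 0.2438) = 2.60 stratified. Adjustment makes the interval slightly wider. The power gain comes from removing the attenuation: ln(1.461)/0.2381 = 1.59 against ln(1.521)/0.2407 = 1.74.

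**Carried into planning.** Required events scale with 1/(ln HR)². If the definitive analysis were adjusted but sized from the unadjusted HR, events would be inflated by (ln 1.519/ln 1.496)² = 1.08, (ln 1.521/ln 1.461)² = 1.22 and (ln 1.519/ln 1.407)² = 1.50. With the repeat's rounded HRs against 1.52, the factors are 1.07, 1.18 and 1.48.

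**The case against.** **The article is silent rather than exclusive.** It never says that the Cox model is unadjusted, and an analysis plan not shown here may list its covariates. This stands as a limit on certainty. It does not remove the point, because the article itself allocates the adjustment and places it with the other models.

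**The unadjusted HR is not wrong under randomisation.** It estimates a marginal effect, while the adjusted HR estimates a conditional one. This stands: the attenuation is relative to the within-stratum effect. For a definitive trial analysed by an unadjusted log-rank test, the marginal HR would be the matching planning input; for an adjusted analysis it errs toward a larger trial.

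**The size rests on assumptions and is small beside sampling error.** This also stands. At stratum HR 0.7 the difference is negligible. The shift in log HR is 0.015, 0.040 and 0.077 across the three scenarios, against a standard error of about 0.24 in a single trial of 80.

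**Stronger readings to avoid.** A reader might infer that leaving out the stratum widens the confidence interval. It does not: the unadjusted model SE was the smaller one in every scenario. A reader might also infer that centre and baseline EQ-5D-5L are left out of every model and of the QALY comparison. The text does not support that. The open-ended covariate clause can cover centre and baseline values for the regression outcomes. The QALY description is a condensed one, and the cost-effectiveness section refers to the methods of a definitive trial.

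**Conclusion.** The point holds, with modest impact. As written, ulcer-size adjustment does not reach the healing-time analysis, although ulcer size is the stratification factor and was chosen for its link with healing. The consequence is an HR closer to 1 than the within-stratum effect and some loss of power. With a moderate to strong stratum effect, the unadjusted test can also be conservative. At a within-stratum HR of 1.5 this ranges from almost nothing (stratum HR 0.7: HR lower by about 0.02, power by about 0.02) to clear (stratum HR 0.33: HR lower by about 0.11, power by about 0.13). Which end applies depends on a prognostic strength the article does not state.

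No success criterion uses the HR, and healing time is a secondary, exploratory outcome. The reason to act is that the estimate may inform the definitive trial's primary outcome and sample size, and the placement of the adjustment does not match the randomisation.

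**What to change.** State in the Statistical analysis section that the Cox model for healing time is adjusted for, or stratified by, the randomisation ulcer-size stratum (1 to 3 cm versus above 3 cm), and that a stratified log-rank test accompanies the Kaplan-Meier curves. Justify this by consistency with the randomisation and by removal of the attenuation, not by narrower intervals.

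The change is one sentence, and the stratum is already recorded for every randomised patient. The price is a slightly larger model SE (0.240 to 0.242 adjusted, or 0.243 to 0.245 stratified, against 0.238 at HR 1.5) and an HR interpreted conditional on ulcer size. When the HR is used to size the definitive trial, the authors should say which of the two it is and match it to that trial's planned analysis. If the full analysis plan already specifies the stratum, only the article's wording needs to be brought into line.

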### Criteria for success

This feasibility trial will be deemed successful and lead to the development of a proposal for an adequately powered randomised controlled trial if:(i)An appropriate primary outcome variable is defined(ii)At least 67 % of randomly assigned patients in the exercise group are compliant with the intervention (defined as at least 75 % of the scheduled sessions are completed as planned)(iii) Loss to follow-up at 12 months is less than 20 %(iv) Patient preferences are not so strong that they result in the conclusion that a randomised controlled trial is not a feasible design.

The criteria for success will provide the basis for interpreting the results of this study and determine whether it is appropriate to proceed to a full trial and (if appropriate) what modifications need to occur for a full trial to be feasible.

### Project management

The management of this study will be the responsibility of the research management group, consisting of the chief investigator (MK), all co-applicants (including GT, HC, JM and AG) and all research staff. Operational management will be the responsibility of the research team consisting of the chief investigator, the principal investigator in Lincoln (GM) and research staff, meeting once a week to ensure adherence to planned timescale, adherence to the intervention and detailed plans for data management and analysis. A trial steering committee consisting of independent clinical ([name] and [name]) and academic members ([name] and [name]) and the chief investigator (MK) will also meet at least twice a year. This committee is responsible for the overall management and oversight of the trial. Because of the low-risk nature of this trial (both treatments being assessed were already being used routinely in clinical practice), we did not judge it necessary to have a separate Data Monitoring and Ethics Committee to oversee the trial. This study was co-adopted to the Primary Care and Dermatology specialities of the UK Clinical Research Network Portfolio (UKCRN ID 16665), which provides research infrastructure resources, including Research Nurse support for recruitment.

